#### Blood Samples Collection

Blood samples will be collected at rest after an overnight fast (>12 h) from an antecubital vein in different tubes containing thixotropic gel, sodium heparin and ethylenediaminetetraacetic acid (EDTA) (BD Vacutainer, Stockholm, Sweden). Samples will be collected at least 72–96 h apart from any exercise or testing session. Samples collected in the sodium heparin and EDTA tubes will be immediately centrifuged (1200 *g*, 10 min and 4°C) whereas thixotropic gel tubes will be kept at room temperature (22–24°C) for 30 min before being identically centrifuged. Samples will be analyzed immediately for routine clinical chemistry measurements and then, they will be put into 500-μL aliquots and frozen at −80°C for later analysis. This further analysis will determine the circulation levels of biomarkers related with oxidative stress, inflammation, anabolic and catabolic processes, neuromuscular remodeling and stress-induced processes. More specifically, oxidative stress will be determined through immunoblot detection of protein carbonylation with commercially available kits, levels of interleukin-6, tumoral necrosis factor alpha (TNFα), and C-reactive protein will be assessed as inflammatory markers and the testosterone: cortisol ratio, growth hormone, insulin growth factor-1, and creatine kinase will be analyzed as biomarkers of anabolic and catabolic processes with a high-sensitivity magnetic multiplex assay (Bio-Plex Multiplex System, Bio-Rad, CA, United States). Furthermore, C-terminal agrin fragment (CAF), as a neuromuscular remodeling biomarker, and growth differentiation factor (GDF-15) as a biomarker for stress-induced processes will be determined using commercially available enzyme-linked immunosorbent assay (ELISA) kits according to the manufacturer’s protocol. All samples collected for a given individual will be assessed within the same sample plate.

### Harms

Interventions and procedures considered in this study are minimally invasive, with a low risk of adverse events. Participants may develop delayed onset muscle soreness during the first sessions, diminishing after few sessions due to the repeated bout effect (Byrne et al., 2006). Since the exercise will be directly supervised by an experienced sport scientist, the risk of injury is minimal. Potential acute or persistent exercise-related adverse events will be brought to the attention of a study physician and discussed with both the participant and the project leader before making joint, informed decisions concerning their treatment and the further participation in the study.

### Statistical Analysis

Data will preferentially be presented as mean ± standard deviation. Normality of distribution will be assessed by the Shapiro–Wilk test and log-transformed in case of non-normal distribution. As preference, the outcomes will be registered as the absolute (Post – Pre) and relative [(Post – Pre)/Pre] change during the 8-week control period and the 12-week PRT program. Given the hierarchical structure and correlated data contained in our investigation (each participant will contribute to observations in two different groups), the existence of partially paired data must be considered for comparison purposes. Thus, linear mixed effect models will be used to assess the goals proposed for the present investigation. To assess the adaptations provoked by two volume × load-matched PRT programs using heavy vs. light loads in older adults (goal 1), changes noted in the legs undergoing HL-PRT and LL-PRT (i.e., week 20-week 8) and those noted in the same legs during the control period (i.e., week 8-week 0) will be compared with treatment (HL-PRT vs. LL-PRT vs. control) as a fixed factor, participants as a random factor and baseline values as a covariate. To investigate the adaptations provoked by heavy- vs. light-load PRT on the contralateral limb in older adults (goal 2), changes noted in the contralateral non-exercising legs of those legs performing either HL- or LL-PRT (i.e., week 20-week 8) and those noted in the same legs during the control period (i.e., week 8-week 0) will be compared with treatment (HL-PRT vs. LL-PRT vs. control) as a fixed factor, participants as a random factor and baseline values as a covariate. The models will be calculated considering maximum likelihood estimation and the best-fitting covariance structure. Bonferroni corrections will be applied for the *post hoc* pairwise comparisons and the Cohen’s *d* effect sizes will be calculated and classified as trivial (0.20), small (0.20–0.49), moderate (0.50–0.79), and large (>0.8) (Cohen, 1988). Potential adverse events and drop-outs will be compared between groups by Chi-squared tests. All statistical analyses will be performed using IBM SPSS Statistics for Windows Version 24.0 (IBM Corp. Armonk, NY, United States), and the level of significance will be set at α = 0.05.

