## Methods/Design

### Experimental Approach

The present project and study protocol were registered in clinicaltrials.gov (ID: NCT03724461, October 30th, 2018) and approved by the Clinical Research Ethics Committee of the Complejo Hospitalario de Toledo (Spain). The study protocol will be conducted following the SPIRIT (Standard Protocol Items: Recommendations for Interventional Trials) statement (Chan et al., 2013). The intervention and data collection will be conducted at the University of Castilla-La Mancha, Toledo (Spain). This is a within-person randomized trial, including an 8-week control period followed by 12 weeks of PRT (Figure 1). The mean changes observed during the 8-week control period will be quantified to determine the possible extent of spontaneous changes in all outcome measures. After completing the control period, the participants will be randomized to one of the following study arms based on the treatment applied to their lower-limbs during the 12-week PRT program: (i) one leg will perform a light-load PRT and the other leg will not perform any exercise; (ii) one leg will perform a heavy-load PRT and the other leg will not perform any exercise; and (iii) one leg will perform a heavy-load PRT and the other leg will perform a light-load PRT. Assessments will be conducted at baseline (week 0), at the end of the control period (week 8), and following the 12-week PRT (week 20).

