### Participants

The sample size was determined by an *a priori* power analysis using G^∗^Power v3 software for MS Windows^®^ (Faul et al., 2007). The effect size value used for calculations was *d* = 0.25 based on a previous study comparing peak power adaptations after a 12-week heavy- vs. light-load PRT in older adults (de Vos et al., 2005). Then, we considered three levels for the between-subject factor (i.e., one for each study arm) and three levels for the within-subject factor (i.e., three repeated measures) setting the alpha error probability at 0.05, a 1−β of 0.95 and assuming a correlation among repeated measures of *r* = 0.8. The model indicated a minimum total sample size of 24 individuals, but considering a 25% dropout rate, we have decided to enroll at least 30 participants in total. People aged 65 years and over, non-institutionalized and without serious mobility limitations will be encouraged to participate. Principally, the volunteers will be recruited among participants involved in non-exercise studies previously conducted by our research group, local advertisements posted in public places and informative talks about healthy aging. After accepting to participate, the volunteers will undergo a physical examination by a geriatrician. The criteria for exclusion are: (i) frailty status (Fried et al., 2001) or low levels of physical function (i.e., Short Physical Performance Battery <7 points) (Guralnik et al., 1994), (ii) neurological, musculoskeletal, or other disorders that might preclude subjects from completing the resistance training and all performance tests, (iii) uncontrolled hypertension, unstable or exercise-induced angina pectoris or myocardial ischemia or any other medical condition that would interfere with testing or increase subjects’ risk of complications during exercise, (iv) history of regular resistance exercise during the previous 3 years, and (v) total or partial knee replacement (i.e., prosthesis). All participants will be informed orally and in written form about the purpose, procedures, benefits, risks, and potential discomfort related to study participation before signing a consent form. This study will be conducted in accordance with the Helsinki declaration.

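### Training-vs-control contrasts compare two changes of the same leg that share the week 8 value, and the stated mixed model does not secure the negative correlation this creates

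*Protocol article*

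**What the plan says.** All of this is in the protocol article.

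- **Response.** Under Statistical Analysis, goal 1 compares "changes noted in the legs undergoing HL-PRT and LL-PRT (i.e., week 20-week 8) and those noted in the same legs during the control period". Goal 2 does the same for the contralateral non-exercising legs.
- **Model.** Both goals use "treatment (HL-PRT vs. LL-PRT vs. control) as a fixed factor, participants as a random factor and baseline values as a covariate". No leg term and no period-within-leg term is named. The stated reason for a mixed model is that each participant contributes observations to two groups; the shared week 8 value is not mentioned.
- **Estimation.** "The models will be calculated considering maximum likelihood estimation and the best-fitting covariance structure". The level at which the structure applies (participant, leg or period) is not given.
- **Error level.** "the level of significance will be set at α = 0.05", and "Bonferroni corrections will be applied for the *post hoc* pairwise comparisons". With three treatment levels there are three pairwise comparisons, so 0.05/3 = 0.0167 each.
- **Correlation.** The sample-size paragraph under Participants works by "assuming a correlation among repeated measures of *r* = 0.8", one value for all pairs of the three visits.

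**The concern.** For one leg the two responses are Y8 - Y0 (control period) and Y20 - Y8 (training period). A chance high value at week 8 raises the first and lowers the second, so the responses are negatively correlated. The training-vs-control contrast is the difference between them, and a negative correlation makes that difference more variable than independence would suggest.

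A participant random intercept implies a correlation of zero or more between observations of one person. Faced with negative correlation, its variance is usually estimated at zero, the changes are treated as independent, and the standard error is too small. The statements that training works and that cross-education occurs both rest on these contrasts.

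The same intercept also has to carry the positive correlation between the two legs in the arm that trains both. When it is estimated at zero, that pairing is lost for heavy- vs light-load training (HL vs LL).

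**Working it through.** **1. The plan's own correlation.** The stated minimum of 24 participants reproduces from a within-between interaction in repeated-measures ANOVA, with 0.25 entered as f, 3 arms, m = 3 visits and a common correlation of 0.8. Noncentrality = 0.25² × 24 × 3/(1 - 0.8) = 22.5 on 4 and 42 df, power 0.965; 21 participants give 0.933. So the plan's working assumption is equal correlation r = 0.8 between visits.

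**2. Correlation of the two changes** (equal variance s²).
- Cov(Y8 - Y0, Y20 - Y8) = s²(r - 1 - r + r) = -(1 - r)s². Each change has variance 2(1 - r)s². Correlation c = -0.5, whatever r is.
- After adjusting each change for its own period's starting value: c = -r²/(1 + r) = -0.64/1.8 = -0.36.
- Under AR(1) over visits: c = -(1 - r)/2 = -0.10 unadjusted, and 0 after that adjustment.

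**3. Error rate if the changes are treated as independent.** With V = true variance/assumed variance of the contrast, type I error = 2[1 - Φ(z/√V)]. If a set of legs is compared only with its own control period, V = 1 - c:

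| c | V | at 0.05 | at 0.0167 |
|---|---|---|---|
| -0.5 | 1.50 | 0.110 | 0.051 |
| -0.36 | 1.36 | 0.092 | 0.040 |
| -0.10 | 1.10 | 0.062 | 0.022 |

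**4. The trial's layout, 24 participants, 8 per arm.** Variances are in units of one change's variance. ρ is the between-leg correlation, which the document does not give.
- *Goal 1:* 16 HL changes against 32 pooled control changes. Assumed variance = 1/16 + 1/32 = 0.0938. True variance at c = -0.5 is 1/16 + (32 + 16ρ)/1024 + (16 + 8ρ)/512 = 0.125 + ρ/32. With ρ = 0, V = 1.33 and the error is 0.090; with ρ = 0.5, V = 1.50 and 0.110; with ρ = 0.9, V = 1.63 and 0.125.
- *Goal 2:* 8 changes against 16. Assumed = 1/8 + 1/16 = 0.1875. True = 0.1875 + 2 × 0.5/16 = 0.25. V = 1.33, error 0.090.
- *HL vs LL, goal 1:* assumed = 2/16 = 0.125, true = 0.125 - ρ/16. With ρ = 0.5, V = 0.75 and the error is 0.024, which is conservative.

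**5. Simulated null trials of the random-intercept model.** Maximum likelihood, intercept variance not below zero, residual-type df.
- 24 or 30 participants, r = 0.8, ρ = 0.5, 2,000-2,500 runs. Goal 1 training vs control: 0.10-0.13 at 0.05 and 0.044-0.064 at 0.0167. Goal 2: 0.09-0.12 at 0.05. The intercept was zero in 87-98% of goal 1 runs. REML instead of ML: 0.09-0.13 for goal 1.
- 30 participants, r = 0.8-0.9, 1,000 runs: 0.105-0.131 (goal 1) and 0.078-0.095 (goal 2) at 0.05; 0.025-0.061 at 0.0167.
- ρ varied from 0 to 0.9 at r = 0.8: 0.08-0.14.
- AR(1) with 0.8: about 0.07-0.10. Step 3 gives only 0.050-0.062 there, so much of that excess must come from other features of the fit, such as ML variances and small numbers, rather than from the shared week 8 value.
- HL vs LL, goal 1, r = 0.8, ρ = 0.5: about 0.03.

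**6. With a covariance allowing negative correlation between periods and correlation between legs** (24 participants, 500 runs): training vs control 0.04-0.07 by ML and 0.04-0.05 by REML at 0.05; 0.012-0.022 at 0.0167. A leg-level correlation plus participant intercept, with nothing across periods, still gave 0.08-0.10.

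**The case against.** The strongest reply is that the plan does not commit to a bare intercept. A single intercept offers no structure to choose, so a promise to pick the best-fitting one has content only if it refers to residual covariance. If the candidates include a structure across periods within leg, selection by fit largely works for goal 1. With AIC selection (30 participants, r = 0.8, 300 runs per setting, Monte Carlo SE about 0.01), the bare intercept won in 0-1% of goal 1 and 4% of goal 2 trials. Goal 1 error was 0.068 and 0.055, against 0.12 and 0.11 under the bare intercept. Goal 2 error was 0.09 and 0.053, against 0.10 and 0.07.

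This stands as far as it goes: the phrase permits a cure. It does not secure one. The article fixes response, fixed factor, random factor, covariate and estimator, describes the dependence only as people contributing to two groups, and names no leg or period level. A natural reading, correlation within leg or person only, leaves the error inflated. For goal 2 the missing leg level is immaterial, since each participant contributes one untrained leg, but the missing period structure is not.

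It is also fair that c = -0.5 needs equal correlation across unequally spaced visits, that 0.8 is a planning assumption, and that between-leg correlation is not given.

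Three further criticisms are tempting and not supported. The log-transform rule precedes the sentence on change scores and can be read as applying to raw positive values. Baseline may mean each period's own starting value, which is an ambiguity. ML rather than REML barely alters the error rates above.

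**Conclusion.** The concern holds for training vs control (goal 1) and contralateral leg vs control (goal 2). If the fitted model is a participant random intercept with independent residuals, type I error is about 0.08-0.13 instead of 0.05 and about 0.03-0.06 instead of 0.0167. This rests on equal variances, a common correlation of 0.8-0.9, and moderate to high between-leg correlation. Under AR(1) it is about 0.07-0.10 at 0.05. With a suitable residual structure it is close to nominal.

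A reader might infer that the plan's error rates are certainly doubled. The text does not support that, because the covariance structure is left open. A reader might also infer that the main comparison, heavy vs light load, is anti-conservative. It is not: for goal 1 it is conservative (0.018-0.031 in simulation at 0.05), so the cost there is lost precision. How much power is lost is not established. The available comparison (0.57-0.63 under the plan, 0.75 for a week-8-adjusted model, at an assumed 0.5 SD) is not size-matched, since the alternative rejected 7.6% under the null with approximate df.

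**What to change.** Replace the stacked change scores.

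- **Training vs control, and goal 2 vs control.** Model the week 0, 8 and 20 values of each leg, with leg nested in participant and an unstructured covariance over time (or another that permits negative correlation between the changes). Test (week 20 - week 8) - (week 8 - week 0). To the same end, compute that difference for each leg and analyse it with a participant random effect; this gave 5.6-5.9% type I error in simulation. It compares each leg with its own control period.
- **HL vs LL.** Model the week 20 value with the week 8 value as covariate and a participant random intercept, using REML and Satterthwaite degrees of freedom. The 7.6% rejection with approximate df is the reason for specifying Satterthwaite. A separate model is preferable: in the runs of step 6, HL vs LL rejected 0.06-0.09.

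No new data are needed, and the models are available in the software the plan names. The analysis section becomes slightly longer. Training-vs-control confidence intervals become wider: with V of 1.33 to 1.50 as in step 4, by a factor of √1.33 = 1.15 to √1.50 = 1.22. That widening is the correction itself.

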**Methods:**

At least 30 well-functioning older participants (>65 years) will participate in a within-person randomized controlled trial. After an 8-week control period, the effects of two 12-week PRT programs using light vs. heavy loads will be compared using an unilateral exercise model through three study arms (light-load PRT vs. non-exercise; heavy-load PRT vs. non-exercise; and light- vs. heavy- load PRT). Muscle-tendon function, muscle excitation and morphology and physical function will be evaluated to analyze the load-specific effects of PRT in older people. Additionally, the effects of PRT will be examined on a non-exercised contralateral limb.

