### Randomization and Allocation of Participants

After completing the control period, the participants will be stratified by their sex and 1RM values and randomly allocated in equal numbers to the three intervention groups. Then, the treatment applied to the subjects’ legs will be determined by coin toss.

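### The contrasts against control compare 12-week training changes with an earlier, pre-randomisation 8-week change in the same legs, and the randomised trained-versus-non-exercised leg contrast is left out of goal 1

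*Protocol article*

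**What the plan says.** The abstract names "three study arms (light-load PRT vs. non-exercise; heavy-load PRT vs. non-exercise; and light- vs. heavy- load PRT". Under Experimental Approach, arm i is described as "one leg will perform a light-load PRT and the other leg will not perform any exercise" and arm ii as "one leg will perform a heavy-load PRT and the other leg will not perform any exercise"; in arm iii one leg trains heavy and the other light. Everyone follows the same order, "including an 8-week control period followed by 12 weeks of PRT", with assessments at weeks 0, 8 and 20.

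Randomisation comes after the control period: "After completing the control period, the participants will be stratified by their sex and 1RM values and randomly allocated in equal numbers". Within each person, "the treatment applied to the subjects’ legs will be determined by coin toss".

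The Statistical Analysis section fixes one linear mixed model per goal. Goal 1 takes the week 8 to week 20 changes in trained legs; goal 2 takes the same changes in the non-exercising legs. In each case these and "those noted in the same legs during the control period (i.e., week 8-week 0) will be compared with treatment" (HL-PRT, LL-PRT or control) as the fixed factor, participant as the random factor and the baseline value as covariate. Bonferroni-corrected pairwise comparisons follow. No other efficacy comparison is described.

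**The concern.** The article presents a within-person randomised trial, and two of its three arms pair a trained leg with a non-exercised leg chosen by coin toss. That pairing gives a comparison over the same 12 weeks, in the same person, under the same season, diet and activity. The analysis does not use it. The only untreated comparator in either model is an interval that came earlier, was shorter and preceded randomisation.

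At stake are two kinds of statement: that either form of training improves an outcome at all (goal 1), and that cross-education occurs at all (goal 2). Both would rest on a before-after comparison, and the bias could run in either direction.

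**Working it through.** **Which changes enter which model**

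| Model | Training-period data | Control data |
|---|---|---|
| Goal 1 | trained legs, weeks 8–20 (12 weeks) | same legs, weeks 0–8 (8 weeks) |
| Goal 2 | non-exercised legs, weeks 8–20 (12 weeks) | same legs, weeks 0–8 (8 weeks) |

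Trained and non-exercised legs appear together in neither model. Every control observation comes from the first period and lasts 8 weeks; every HL-PRT or LL-PRT observation comes from the second and lasts 12. Period and length are therefore aliased with treatment versus control, and neither the participant effect nor the baseline covariate can separate them. HL-PRT versus LL-PRT lies wholly within the second period, so it escapes this.

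**The plan's own figure.** The stated minimum of 24 participants can be reproduced as an arm-by-time interaction with 0.25 read as Cohen's f: 23, or 24 in equal arms (power 0.965). That calculation has no control-period contrast and does not bear on this point.

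**Size of the bias.** The documents give no drift, so the values here are assumptions.
- Linear drift g per week, no treatment effect: 12g - 8g = 4g. With 4% over 8 weeks, g = 0.5% and the bias is 6% - 4% = +2%.
- The same 4% as one-off learning, complete by week 8: 0% - 4% = -4%.
- Control change scaled by 12/8: 4% × 1.5 = 6%. The bias is 6% - 6% = 0 under linear drift, but 0% - 6% = -6% under one-off learning.

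**Effect on false positives.** This is a paired t approximation for one load in goal 1, with 20 legs (10 from the single-load arm, 10 from arm iii), the protocol's r = 0.8 and equal correlation across visits. A change has variance 2(1 - 0.8) = 0.40. Consecutive changes share week 8, so they correlate at -0.5, and their difference has variance 2 × 0.40 × 1.5 = 1.20. The SE is sqrt(1.20/20) = 0.245 SD.

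| Assumed drift (SD/week) | Bias 4g (SD) | Type I error |
|---|---|---|
| 0.01 | 0.04 | 5.3% |
| 0.02 | 0.08 | 6.1% |
| 0.03 | 0.12 | 7.5% |
| other order effects | 0.20 | 12% |

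**Precision of the omitted contrast.** Trained minus non-exercised at week 20, adjusted for week 8, has residual variance 1 - 0.8² = 0.36 per leg. With an assumed between-leg correlation of 0.5 and 10 pairs per arm, SE = sqrt(2 × 0.36 × (1 - 0.5)/10) = 0.19 SD. With 25% dropout, 8 or 7 pairs give sqrt(0.36/8) = 0.21 or sqrt(0.36/7) = 0.23 SD. In simulation under the same assumptions without dropout, the planned HL-versus-control estimate had a standard deviation of about 0.19 to 0.22 SD, depending on baseline adjustment, and the paired adjusted contrast about 0.20 SD. The randomised contrast is therefore of similar precision, but each arm is small: 10 pairs detect a standardised paired difference of about 1.00 at 80% power, and 8 or 7 pairs about 1.16 or 1.27.

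**The case against.** **The control period is deliberate.** The Introduction recommends one to account for measurement error, biological variability and the effect of testing, and Experimental Approach uses it to gauge spontaneous change. This stands as a reason to keep the period. It does not make an earlier 8-week change equivalent to a concurrent 12-week one.

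**The non-exercised leg is not a clean control.** The Discussion expects cross-education, so trained minus non-exercised estimates the training effect less any cross-education. That is a different quantity and understates the total effect if the other leg gains. This also stands. It argues for reporting both contrasts with their meanings stated; the article gives no reason for omitting one.

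**The arm labels may only describe what each leg receives.** That is a fair reading, and both kinds of leg are used, one kind in each goal. The point does not depend on the labels: the coin toss creates the randomised contrast whatever it is called.

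**Test learning is limited.** At least two familiarisation sessions precede baseline. They should reduce learning, but they do not touch season or the 8-versus-12-week difference.

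**Stronger readings a reader might infer.** One is that both goals fail. They do not, because the main comparison of loads is randomised and equal in length in both models. Another is that the trial holds a randomised test of whether cross-education exists and neglects it. It does not: every participant trains at least one leg, so this is a limit of the design. Regression to the mean is also tempting, but the article describes no selection on extreme primary-outcome values.

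**Conclusion.** The point holds for the contrasts against control only. They are non-randomised before-after comparisons over unequal intervals, and for goal 1 a concurrent randomised contrast is available but not planned. The bias is 4 weeks of drift if change is linear, and the opposite sign if early gains are one-off learning. For assumed drifts of 0.01 to 0.03 SD per week the distortion of type I error is modest (5.3% to 7.5%); it reaches 12% only at an assumed bias of 0.20 SD. The aliasing follows directly from the article's text; the sizes rest on the assumed drift, equal correlation across visits and, for precision, the assumed between-leg correlation.

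The consequence is greatest for goal 2. Whether cross-education occurs depends wholly on the control-period contrast, and the Discussion anticipates little or no difference between loads there. A separate analysis plan may add contrasts, but the article specifies the model for each goal explicitly. The change is advisable and inexpensive.

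**What to change.** 1. **Goal 1.** Add the within-person contrast of trained minus non-exercised leg at week 20, adjusted for week 8, separately in arm ii (HL-PRT) and arm i (LL-PRT). Report it beside the control-period contrast, and state that it estimates the training effect net of any cross-education and so is conservative for the total effect.
2. **Both goals.** Label every control-period contrast as a non-randomised before-after comparison over unequal intervals.
3. **Goal 2.** Rest inference on the HL versus LL contrast between untrained legs, which the model already contains. Word any claim that cross-education occurs as non-randomised evidence, and say that no concurrent untreated comparator exists.
4. **Sensitivity, if wanted.** Show a control change scaled by 12/8 only as a linear-drift scenario, beside the unscaled result, because scaling worsens the bias if the control-period change was one-off learning.

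The cost is a few extra contrasts on measurements already scheduled and more cautious wording. Nothing changes in data collection or in the interventions.

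### The only covariate for the heavy-vs-light comparison is the baseline value, defined as week 0, although randomisation and the training change start at week 8

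*Protocol article*

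**What the plan says.** **Visits.** Protocol article, Experimental Approach: "Assessments will be conducted at baseline (week 0), at the end of the control period (week 8), and following the 12-week PRT (week 20". This is the only place where baseline is tied to a visit.

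**Randomisation.** The article places allocation at the end of the control period: "After completing the control period, the participants will be stratified by their sex and 1RM values and randomly allocated in equal numbers" (section Randomization and Allocation of Participants). The value at randomisation is therefore the week 8 value.

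**Goal 1 model.** Statistical Analysis compares "changes noted in the legs undergoing HL-PRT and LL-PRT (i.e., week 20-week 8" for the training period with "those noted in the same legs during the control period (i.e., week 8-week 0" for the control period. Treatment (heavy, light, control) is the fixed factor, with "participants as a random factor and baseline values as a covariate". Goal 2 repeats this for the untrained contralateral legs.

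**Covariance.** "The models will be calculated considering maximum likelihood estimation and the best-fitting covariance structure".

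**Planning correlation.** Participants: "assuming a correlation among repeated measures of" r = 0.8, one value for all pairs of visits.

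Statistical Analysis also defines change by a period-specific 'Pre' value, which is week 0 for the control period and week 8 for training. It does not equate this with the baseline covariate.

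**The concern.** A covariate in a randomised comparison of changes earns its place by predicting the change and by correcting chance imbalance at the start of treatment. The natural candidate for the training change is the leg's week 8 value. With baseline taken as week 0, the model adjusts instead for a value measured eight weeks before randomisation. One covariate slope is also shared by two kinds of rows, control changes that start at week 0 and training changes that start at week 8.

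The stakes are precision in arms of about 10, and how far a chance difference between heavy and light legs at week 8 carries into the estimate.

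**Working it through.** **The plan's own figure.** The stated minimum of 24 reproduces with the repeated-measures interaction test. Here λ = f²·N·m/(1−ρ) = 0.0625 × 24 × 3 / 0.2 = 22.5, with df 4 and (24−3) × 2 = 42, giving power 0.965. The formula first reaches 0.95 at N = 23, which rounds to 24 for three equal arms. It takes ρ = 0.8 as a common correlation and contains no covariate, so the point below does not change the sample size. (It reproduces only with 0.25 entered as Cohen's f, although the article labels it d; that is a separate matter.)

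**Inputs below.** Outcome variance 1 at each visit; ρ = 0.8 for all pairs (Participants). Y0, Y8 and Y20 are a leg's values at weeks 0, 8 and 20.

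**Residual variance of the training change Y20−Y8**
- No covariate: 2(1−0.8) = 0.400.
- Week 0: the covariance with the change is 0.8−0.8 = 0, so the residual variance stays 0.400.
- Week 8: the covariance is 0.8−1 = −0.2, so the residual variance is 0.400−0.04 = 0.360 (10% lower).
- Both: 1−2(0.64)/(1+0.8) = 0.289. This is 28% below week 0 alone and 20% below week 8 alone.

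**Common slope.** On week 0, the control change Y8−Y0 has slope 0.8−1 = −0.2 and the training change has slope 0. One shared slope fits neither.

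**What the control-period rows can recover.** The covariance of the two consecutive changes is 0.8−1−0.8+0.8 = −0.2, so their correlation is −0.2/0.4 = −0.5. Given Y0, the control change has variance 0.4−0.04 = 0.36. Conditioning the training change on it as well leaves 0.4−0.04/0.36 = 0.289, the same as adjusting for both values. A covariance structure that carries this correlation therefore recovers the information. A participant random intercept cannot, because its variance cannot be negative. In simulated goal 1 trials with a week 0 covariate it was estimated at zero in 98%.

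**Simulated SD of the heavy-minus-light estimate, 10 per arm**

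| Analysis | Goal 1 | Goal 2 |
|---|---|---|
| Training change, week 0 covariate | 0.165 | – |
| Training change, week 8 covariate | 0.157 | – |
| Training change, both covariates | 0.140 | 0.258 |
| Stated model, week 0 covariate, unstructured leg-by-period covariance | 0.139 | 0.257 |
| Stated model, week 0 covariate, correlation not modelled | 0.177 | 0.296 |

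Goal 1 assumes a between-leg correlation of 0.5. Its 0.177 also ignores the correlation between a person's two legs. Among the training-change rows, (0.140/0.165)² = 0.72, a 28% reduction. In goal 2, (0.258/0.296)² = 0.76, a 24% reduction. A further simulation with assumed variance components (person 0.65, leg 0.15, person-visit 0.10, residual 0.10) gave 27% for goal 1 and 22% for goal 2. Adding an assumed individual-response variance of 0.2 lowered these to 17% and 11%.

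**Sensitivity to the correlation pattern** (assumed values for weeks 0–8 / 0–20 / 8–20)

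| Pattern | Week 0 | Week 8 | Both | Both vs week 0 |
|---|---|---|---|---|
| 0.8 / 0.64 / 0.8 | 0.374 | 0.360 | 0.360 | −4% |
| 0.9 / 0.8 / 0.85 | 0.290 | 0.278 | 0.271 | −6% |
| 0.8 / 0.7 / 0.8 | 0.390 | 0.360 | 0.350 | −10% |
| 0.85 / 0.75 / 0.8 | 0.390 | 0.360 | 0.342 | −12% |

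**Chance imbalance at week 8.** Subtraction fixes the slope of week 20 on week 8 at 1, whereas its expected value is 0.8, so 0.2 of any imbalance remains in the estimate.
- Goal 2 compares about 10 with 10 independent legs. The imbalance SD is √(2/10) = 0.45, and a one-SD imbalance leaves 0.09 SD.
- Goal 1 has 20 legs per treatment, ten of them paired within persons. With the components above, the imbalance variance is (10 + 10 + 10 × 2 × 0.25)/400 = 0.0625, so the SD is 0.25 and 0.05 SD remains.
- Both figures ignore stratification by sex and 1RM.

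**The case against.** The strongest reply is that nothing need be lost. The control-period changes of the same legs are outcome rows in the same model, so both pre-training values are in it, and the covariance is to be chosen by fit. With an unstructured leg-by-period covariance the stated model matches adjustment for both values (0.139 against 0.140; 0.257 against 0.258). This stands. A reader might infer that the plan throws away one of its two pre-training measurements; the documents do not support that. The loss is conditional on a structure that misses the negative correlation. What remains is that the article names only a participant random factor, which cannot carry it, and leaves the rest to a choice made on the data.

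Second, baseline may mean each period's own start, by analogy with 'Pre'. That is a possible reading, but the text does not state it, and the one timed definition points to week 0. On that reading the slope problem largely goes, and what is left is the gain from adding week 0 (0.360 against 0.289 at r = 0.8, and none in the 0.8/0.64 pattern).

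Third, a reader might infer that the heavy-vs-light contrast is biased. It is not: allocation at week 8 keeps it unbiased on average, chance imbalance is part of the standard error, and stratification gives some balance. Stratification on 1RM does not directly balance the other outcomes, such as rate of force development or muscle size.

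Finally, a condensed article may leave detail to a fuller plan. A fuller plan that names the visit and the covariance would settle the matter. But the article does name the covariate, and its own definition places that covariate at the wrong visit for the training change.

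**Conclusion.** The point holds as one of precision and clarity. As written, the covariate's only defined time point is not the start of the training change, and at the plan's own r = 0.8 it contributes nothing to the heavy-vs-light comparison. Against adjusting for both pre-training values, the variance given up is at most about 22–28%. It is about 4–12% under the decaying correlations tried, smaller with individual variation in response, and essentially nil if the fitted covariance allows the −0.5 correlation. These sizes rest on equal variances, the planning correlation and assumed variance components; the article gives no data to choose among the patterns. In these checks, adjusting for both values was never appreciably less precise than the alternatives, and it removes dependence on a data-driven covariance choice.

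**What to change.** For heavy vs light, in goals 1 and 2, state in Statistical Analysis that each leg's training change (or week 20 value) is adjusted for that leg's week 8 value of the same outcome, preferably with its week 0 value as a second covariate. Replace the undated baseline term accordingly.

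If the control-period rows stay in the same model, give them the week 0 value only, with its own slope. Week 8 must not be a covariate on those rows, because it is their end value. Prespecify a leg-by-period covariance that allows negative correlation, rather than choosing it by fit.

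The cost is one or two degrees of freedom per outcome and a modest change to the model specification, which is more than a change of wording because the heavy-vs-light contrast is now part of a single three-level treatment model. No new measurements are needed, and the sample size does not change.
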